##### Cell Isolation

PBMCs (peripheral blood mononuclear cells) will be isolated from peripheral venous blood (90 ml EDTA blood) by centrifugation on a Lymphoprep™ (Fresenius Kabi Norge AS) density gradient. Purified PBMC will be aliquoted and cryo-preserved in liquid nitrogen for at least 4 weeks before analysis (except for the assessment of immune cell composition, where freshly isolated cells will be used).

CSF will be obtained from patients by lumbar puncture and centrifuged within 30 min. The supernatant will be separated and cells will be used for further analyses.

##### Flow cytometry

The identification and quantification of leukocyte subsets will be done by flow cytometric analysis of PBMCs and CSF cells as described [30]. For intracellular stainings, the BD Cytofix/Cytoperm™ Fixation/Permeabilization Solution Kit with BD GolgiPlug™ will be used (BD Biosciences) according to standard protocols.

Cells will be analysed on a Gallios Flow Cytometer (Beckman Coulter).

##### CDR3 spectratyping

Spectratyping will be performed essentially as described before [31] using a common Vβ nomenclature [32]. Spectratyping data will be processed by GeneMarker Software V1.91 (SoftGenetics). For all PCR products of Vβ- and Cβ-primers the peak intensities will be plotted against the fragment lengths. Unskewed repertoires yield Gaussian length distributions with a high number of detectable peaks, while skewed repertoires show distortions with reduced numbers of fragment lengths. A previous study [33] using capillary electrophoresis revealed maximum peak numbers between 9 and 13 for each individual of the 24 inspected Vβs giving a total of 287 peaks, representing a theoretical complexity of 100 %. The complexity score (CS) will be calculated by quantifying the obtained peaks in every single Vβ of each sample and dividing the peak number through the theoretical maximum.

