e. Spectratyping of the T cell repertoire concerning the expansion of distinct clones:	
- Relative and absolute change from baseline for complexity scores	
- Qualitative comparison of the distribution of CDR3 sequences	
f. Regulatory T-cell function:	
- Relative and absolute change from baseline in production of TGF-beta and IL-10 of CD4^+^CD25^+^FOXP3^+^ regulatory T cells	
- Suppression of T cell proliferation: Relative and absolute change from baseline in responder T cell proliferation assessed by suppression assays	

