Besides quantitative effects, especially the qualitative effects of alemtuzumab reprogramming the immune system might underlie its long-lasting effects. CD4^+^CD25^high^CD127^low^ regulatory T cells have been demonstrated to be relatively increased in the CD4^+^ T cell compartment, although absolute numbers remain low hampering further investigations [7, 8]. Significantly increased levels of the immunoregulatory cytokines TGFβ-1 and IL-10 were observed. Furthermore, Th2 cells dominate the CD4^+^ T cell pool, while pro-inflammatory T_h_ 1 and T_h_ 17 cells are reduced in association with a reduction in IFN-γ, IL-12, IL-17, IL-21, IL-23 and IL-27 serum levels [42]. Jones and colleagues detected an increased expression of the inhibitory receptors PD-1 and LAG-3 on CD4^+^ T cells [7]. Our study intends to confirm and understand the underlying mechanisms of these findings as well as to expand them. Therefore a detailed immune phenotyping of different immune cell subsets and their properties is planned for the peripheral blood as well as the CSF. There has been no investigation of the CSF compartment so far under alemtuzumab treatment; however this promises deeper insight into the immune processes in the CNS.

The functional properties of T cells will be extensively investigated post alemtuzumab treatment including proliferation, cytokine production as well as immune regulatory and cytotoxic propensity. The spatial and functional changes observed over time will help to understand the reprogramming effects of alemtuzumab. The expression profiles of activating or inhibitory molecules on T cells will be assessed to gain insights into the fundamental alterations in immunological networks. The clonal expansion of autoreactive T cells is believed to be critically involved in the local immune reactions in MS [43]. A restoration of T cell diversity might therefore have beneficial effects to MS disease activity and will be assessed by spectratyping over study time.

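### The complexity score counts spectratyping peaks and ignores their height, so it can largely miss the clonal expansion that item 2e is meant to assess; the assay described also gives CDR3 lengths, not sequences.

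*Protocol article*

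**What the plan says.** Table 4 of the protocol article (Secondary endpoints, item 2e) introduces the measure as "Spectratyping of the T cell repertoire concerning the expansion of distinct clones". It has two components. One is numeric: "Relative and absolute change from baseline for complexity scores". The other is descriptive: "Qualitative comparison of the distribution of CDR3 sequences".

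The section on CDR3 spectratyping describes the readout. For each Vβ and Cβ product, "the peak intensities will be plotted against the fragment lengths". The denominator of the score comes from an earlier study, which found "maximum peak numbers between 9 and 13 for each individual of the 24 inspected Vβs giving a total of 287 peaks"; this total is taken as 100 %. The score is then "calculated by quantifying the obtained peaks in every single Vβ of each sample and dividing the peak number through the theoretical maximum". The same section says that "skewed repertoires show distortions with reduced numbers of fragment lengths". It describes no sequencing step.

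The Discussion states the purpose: "A restoration of T cell diversity might therefore have beneficial effects to MS disease activity and will be assessed by spectratyping over study time". It later mentions this diversity analysis as a possible new route to a marker of treatment response.

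**The concern.** When a clone expands, the first effect on a spectratype is that one peak rises. Other peaks disappear only once they fall below whatever level counts as detectable. A score that counts peaks therefore responds late to expansion, and its response depends on the detection cutoff. The article itself links skewing both to a distorted profile and to fewer lengths, but the score uses only the second feature.

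The wording of the descriptive component also goes beyond the assay. A fragment-length profile gives CDR3 lengths. Two clones with the same Vβ and the same length share a peak, so the method as described cannot identify sequences or a distinct clone.

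What is at stake is interpretation. A flat complexity score could be reported as absence of clonal expansion when the score could hardly have shown it.

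**Working it through.** **Denominator.** The article gives 24 Vβs with maxima of 9 to 13 peaks. The possible total runs from 24 × 9 = 216 to 24 × 13 = 312. The stated 287 lies inside this range, with a mean of 287 / 24 = 11.96 per Vβ. The individual maxima are not listed, so 287 can be checked only for consistency. One lost peak is worth 1 / 287 = 0.35 percentage points. If a whole 12-peak Vβ collapses to one peak, the total score falls only to (287 − 11) / 287 = 96.2 %.

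**Model (assumptions, since the article gives neither profile width nor cutoff).** One Vβ has 12 lengths with Gaussian shares p, with SD 2, 2.2 or 2.5 length steps. A clone with share f of that Vβ sits at length j, so the new shares are q = (1 − f)p, plus f at position j. A peak counts if it reaches the cutoff c, a percentage of the tallest peak. The profile shift is ½ Σ|q − p|, which equals f(1 − p_j).

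**Peaks lost against baseline, clone on a central length:**

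| SD | f | c = 0.5 % | 1 % | 2 % | 5 % | Profile shift |
|---|---|---|---|---|---|---|
| 2 | 20 % | 0 | 0 | 2 | 2 | 16.1 % |
| 2 | 50 % | 2 | 2 | 4 | 4 | 40.3 % |
| 2.2 | 20 % | 0 | 0 | 2 | 0 | 16.4 % |
| 2.2 | 50 % | 0 | 2 | 4 | 4 | 41.1 % |
| 2.5 | 20 % | 0 | 0 | 0 | 2 | 16.8 % |
| 2.5 | 50 % | 0 | 0 | 2 | 4 | 42.1 % |

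Example of the shift (SD 2, p_j = 0.1938): 0.2 × 0.8062 = 16.1 % and 0.5 × 0.8062 = 40.3 %. With the clone on an outermost length (p_j = 0.0046), the shifts are 19.9 % and 49.8 %.

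Over all positions the loss never exceeds 2 peaks for the 20 % clone (2 / 287 = 0.7 points) or 4 peaks for the 50 % clone (4 / 287 = 1.4 points). In one corner (20 % clone on an outermost length, 5 % cutoff, SD 2 or 2.2) the count even rises by 1, because the clone lifts a previously undetected peak above the cutoff.

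**Like for like.** The score is expressed over all 287 peaks, while the shift above belongs to one Vβ. Within that Vβ, the loss of 2 or 4 peaks is 2 / 12 = 17 % or 4 / 12 = 33 % at the stricter cutoffs, and nothing at the laxer ones. An intensity index averaged over 24 Vβs is diluted too: 16.1 / 24 = 0.7 points and 40.3 / 24 = 1.7 points. The advantage of intensity is that the shift does not depend on a detection cutoff, and that it can be read per Vβ.

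**Sampling.** With an unchanged repertoire and N T cells spread evenly over 24 Vβs, the expected score is the mean of 1 − (1 − p_i)^(N/24). At N = 1,000 it is 75 % (SD 2) or 85 % (SD 2.5). At N = 50,000 it is 100 %. For blood, the Cell Isolation section gives 90 ml and the Sample size section assumes 100 lymphocytes/μl after treatment: 90,000 μl × 100 = 9 million lymphocytes, before losses, subset fractions and division between assays.

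**The case against.** A reader might infer that spectratyping here yields fragment lengths alone, and that an expanded clone would leave endpoint 2e as a whole unchanged. The documents do not support that. Intensities are plotted against length, a dominant clone would show as a raised peak, and the descriptive component can use that profile. Only the numeric score is blind.

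The zero-loss result also depends on the cutoff. With SD 2 and a 20 % clone on a central length, the smallest peak is about 1.0 % of the tallest, so a 1 % cutoff just keeps it and a 2 % cutoff drops two peaks. Large expansions do lower the score, as the article says. This stands, and is why the result is given as a range.

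A reader might further infer that the score will fall in blood after depletion simply because fewer cells are sampled. That is not shown: about 9 million lymphocytes is far above the 50,000 T cells at which the model gives 100 %. The worry is plausible mainly for CSF, or for small aliquots whose size is not given. Input and minimum-input rules are laboratory detail that an article may leave to its cited method, so their absence is not a fault.

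The cited method is not at hand, so a sequencing step there cannot be ruled out. Finally, making an intensity index the main repertoire measure would be a preference, and such an index is itself noisy at low input.

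**Conclusion.** The point holds for the numeric measure and for the wording. Item 2e names clonal expansion, but its only number is a peak count that can stay still, or move by at most 1.4 percentage points of the total, while half of one Vβ is taken over by a single clone. The sizes rest on assumed Gaussian 12-length profiles and cutoffs of 0.5 to 5 %. That intensity plays no part in the score follows directly from the article's definition.

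The descriptive comparison may reveal such a clone by eye but does not quantify it, and the described assay supports statements about CDR3 length, not sequence. The weight is modest: this is one secondary item in an exploratory study of 15 patients with no significance level set. The correction is still worth making, because the needed data are already recorded.

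**What to change.** - Keep the complexity score and describe it as a measure of repertoire diversity, not of clonal expansion.
- Add alongside it an intensity-based skewing index from the recorded peaks. One example is, per Vβ, half the sum of absolute differences between the sample's length profile and the baseline or reference profile, averaged over Vβs. Show the per-Vβ values as well, since averaging over 24 dilutes a change confined to one.
- In item 2e, replace the reference to sequences by 'CDR3 length distribution', unless sequencing is actually done; if it is, say so in the spectratyping section. State that clones of equal length cannot be separated.
- Read low scores from samples with few T cells, mainly CSF, with caution, because peaks can be lost through sampling alone.

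The cost is an edit to the endpoint wording and a small extra calculation, with no new samples or assays. The index does not remove the low-input problem, so the same caution applies to it.

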##### Migration Assay

Transmigration assays will be performed with minor modifications as described previously [34, 35]. Briefly, transwell inserts will be assembled with HBMEC (human brain microvascular endothelial cells). Human PBMCs (each 5x105) will be transferred to the HBMEC layer for 14 h. Migrated cells from the lower of the two compartments will be collected and Calibrite beads (BD Biosciences) will be added. Next, human cells will be stained for CD4, CD8, CD14, CD19 and CD56, with the respective monoclonal antibodies and relative cell numbers will be determined by flow cytometry.

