4. Medical, psychiatric, cognitive, or other conditions that, in the Investigator’s opinion, compromise the patient's ability to understand the patient information, to give informed consent, to comply with the trial protocol, or to complete the study	
5. Any disability acquired from trauma or another illness that could interfere with evaluation of disability due to MS	
6. Major systemic disease or other illness that would, in the opinion of the Investigator, compromise patient safety or interfere with the interpretation of study results, e.g., current peptic ulcer disease or other conditions that may predispose to haemorrhage	
7. Known bleeding disorder (e.g., dysfibrinogenemia, factor IX deficiency, haemophilia, Von Willebrand’s disease, disseminated intravascular coagulation (DIC), fibrinogen deficiency, or clotting factor deficiency)	
8. Significant autoimmune disease including but not limited to immune cytopenias, rheumatoid arthritis, systemic lupus erythematosus, other connective tissue disorders, vasculitis, inflammatory bowel disease, severe psoriasis	
9. History of malignancy, except basal skin cell carcinoma	
10. Major psychiatric disorder that is not adequately controlled by treatment	
11. Epileptic seizures that are not adequately controlled by treatment	
12. Active infection, e.g., deep-tissue infection, that the Investigator considers sufficiently serious to preclude study participation	
13. In the Investigator’s opinion, is at high risk for infection (e.g., indwelling catheter, dysphagia with aspiration, decubitus ulcer, history of prior aspiration pneumonia or recurrent urinary tract infection)	
14. Seropositivity for human immunodeficiency virus (HIV)	
15. Infection with hepatitis C virus	
16. Past or present hepatitis B infection (positive hepatitis B serology)	
17. Active infection with human cytomegaly virus (HCMV), Epstein-Barr virus (EBV), varicella-zoster virus (VZV)	
18. Latent tuberculosis unless effective anti-tuberculosis therapy has been completed, or active tuberculosis.	
19. Invasive fungal infections in history and at present	
20. Cervical cytology other than PAP I or PAP II (Papanicolaou) or cervical high risk human papillomavirus (HPV) positivity	
21. Any other illness or infection (latent or active) that, in the Investigator’s opinion, could be exacerbated by study medication	
22. CD4^+^ T-cell count (absolute CD3^+^CD4^+^) < lower limit of normal (LLN) at Screening	

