#### Secondary endpoints

Secondary endpoints extend the already mentioned investigations in the peripheral blood and mainly focus on three points: The absolute and relative change from baseline of the aforementioned cell counts in the CSF at indicated time points of sampling (see Additional file 1: Assessment Schedule), functional characterization of T cells in peripheral blood and the CSF at indicated time points of sampling (see Additional file 1: Assessment Schedule) and the evaluation of potential neuroprotective properties of alemtuzumab. A complete listing is found in Table 4.

**Table 4 Tab4:** Secondary Endpoints

1. Absolute and relative change from baseline of cell-counts in the CSF at indicated time-points of sampling (see Additional file 1: Assessment Schedule). The same cell-types as indicated for the primary endpoints will be evaluated.	
2. Functional characterization of T-cells in the peripheral blood and the CSF at indicated time-points of sampling (see Additional file 1: Assessment Schedule):	
a. Activation status of cell surface receptors assessed by flow cytometry: Relative and absolute change from baseline of mean fluorescence intensity (MFI) and of proportion of positive cells regarding CD25, HLA-DR, LFA-1, CD29, CD69, CD71 expression	
b. Expression of co-inhibitory molecules assessed by flow cytometry: Relative and absolute change from baseline of MFI and of proportion of positive cells regarding PD-1 = CD279, ICOS = CD278, TIM-3, CTLA4 expression	
c. Effector functions of CD4 and CD8 positive T cells:	
- Relative and absolute change from baseline of the results of cell proliferation assays assessed as percentage of proliferated cells	
- Relative and absolute change from baseline of cytokine production measurement assessed as concentration	
- Relative and absolute change from baseline of cytolytic activity assessed by flow cytometry measurement of MFI and proportion of positive cells regarding Granzyme B, Perforin and CD107a expression	
- Relative and absolute change from baseline of intracellular calcium response assessed as concentration	
d. Migrational capacity:	
- Relative and absolute change from baseline MFI and proportion of positive cells assessed by flow cytometry expression analysis of CD11a, CD31, CD44, CD49d, CCR5, CCR6, CCR7	
- Absolute and relative change of cell numbers of migrated cells compared to baseline assessed in an in vitro model by flow cytometry analysis	

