## Discussion

Approved for the treatment of active RRMS alemtuzumab has demonstrated a favourable risk-benefit profile under the precautions of an intensive surveillance program. Alemtuzumab leads to a sustained reprogramming of the immune system lasting for at least several years and is associated with considerable adverse events, which necessitate the early recognition for therapy in time. For the best possible risk-benefit ratio deeper insights into the MOA are clearly needed to identify markers for treatment response and adverse event risk.

So far, the mechanism by which alemtuzumab exerts its therapeutic effects in MS is not fully elucidated. Initial clinical trials demonstrated efficiency of alemtuzumab rather in RRMS then SPMS pointing towards effects directed against acute inflammatory processes predominantly driven by adaptive immunity in contrast to neurodegenerative processes partially driven by innate immunity [40]. This is thought to be related to the limited expression of CD52 on innate immune cells leading to resistance to alemtuzumab mediated depletion. A study of Buggins and colleagues (2002) observed a loss of CD52 in tissue-resident human innate immune cells during maturation or differentiation [41]. The relatively unaffected innate immune system as well as the limited immune cell depletion in primary and secondary lymphoid tissues (as observed in humanized CD52 mice [4]) are believed to explain the low incidence of severe or opportunistic infections despite the long-lasting lymphopenia.

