Another focus of our study is on the migrational capacity of T cells after alemtuzumab treatment. It is assumed for MS that autoimmune T cells migrate into the CNS after they have been activated in the periphery [44–46]. A study of Havari and colleagues has recently shown that anti-murine CD52 treatment had no effect on the migratory ability of immune cells [47]. However, since results from animal experiments cannot be easily transferred these findings have to be further evaluated in humans. Moreover, CD52 has been shown to play a role in transendothelial migration of T cells through human umbilical vein endothelial cell monolayers [48].

More uncertainty surrounds the neuroprotective potential of alemtuzumab compared to anti-inflammatory effects. A post hoc subgroup analysis of the CAMMS223 trial demonstrated a significant improvement in EDSS scores even in patients without pre-treatment clinical disease activity (EDSS improvement by 0.31 points, *P* < 0.005) indicating potential neuroprotective effects of alemtuzumab [15]. In vitro experiments with peripheral blood mononuclear cells of alemtuzumab treated patients produced increased amounts of neurotrophins and were able to prolong survival of murine neurons and oligodendrocytes [15]. However, immune cells producing neurotrophins have not been detected in the CNS of alemtuzumab treated patients so far. Moreover, the short half-lives and the inability to pass the blood-brain-barrier (BBB) of neurotrophins argue against an effect of peripherally detected neurotrophic factors in the CNS [49]. Combining longitudinal clinical (SAD, SRD), MRI (brain atrophy, structural integrity) and experimental (neurotrophins and markers for neurodegeneration in the CSF, impact on neuronal networks in vitro) our study intends to evaluate potential neuroprotective properties of alemtuzumab.

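### The listed migration stain has no CD3, so residual CD4-bearing non-T cells cannot be reliably told from migrated T cells, and any residue would weigh more after depletion (minor)

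*Protocol article*

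**What the plan says.** Under Migration Assay, the input is unsorted: "Human PBMCs (each 5x105) will be transferred to the HBMEC layer for 14 h". After migration, "human cells will be stained for CD4, CD8, CD14, CD19 and CD56, with the respective monoclonal antibodies", and relative cell numbers are read by flow cytometry. CD3 is not in the list, and no gating rule is given.

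The readout is item 2d of Table 4: "Absolute and relative change of cell numbers of migrated cells compared to baseline assessed in an in vitro model by flow cytometry analysis". That row does not name the cell type, but its parent item is "Functional characterization of T-cells in the peripheral blood and the CSF at indicated time-points of sampling", and the Discussion says "Another focus of our study is on the migrational capacity of T cells after alemtuzumab treatment".

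Elsewhere, exclusion criterion 22 identifies CD4 T cells with CD3 ("T-cell count (absolute CD3^+^CD4^+^) < lower limit of normal (LLN) at Screening"), and criterion 23 does the same for CD8 T cells. Table 3 lists dendritic cells by CD303, CD11c and CD141, separates non-classical from classical monocytes by lower CD14 and by CD16, and lists natural killer T cells. Apart from CD14, none of these markers is in the migration stain.

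**The concern.** CD4 and CD8 are not exclusive to T cells. As general immunology, which the document does not state, monocytes and dendritic cells carry CD4 and some NK cells carry CD8. The panel includes CD14 and CD56, so most of these cells can be gated out. Two gaps remain without CD3:

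- CD4-bearing cells that are low or negative for CD14 and negative for CD56 cannot be reliably separated from CD4 T cells.
- CD56-positive T cells cannot be told from NK cells, so excluding CD56-positive events drops them too.

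A constant contamination would largely cancel in a change from baseline. This one would not be constant. Alemtuzumab removes lymphocytes far more than innate cells; the Discussion speaks of "The relatively unaffected innate immune system". Part of an apparent change in T-cell migration could then reflect a changed cell mix in the gate.

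**Working it through.** **The plan's own figures.** The plan gives no number for the migration assay. Its only calculation, under Sample size, supplies the before and after lymphocyte counts used here, and it reproduces. The half-width t(0.975, n−1) × SD × √[χ²(0.80, n−1)/(n−1)] / √n gives, for n = 15 and n = 10:

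- before treatment: 283.7 and 375.4 (stated 284 and 375)
- after treatment: 31.5 and 41.7 (stated 32 and 42)
- change: 315.3 and 417.2 (stated 315 and 417)

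**Inputs from the document.** Lymphocytes 2100/µl before and 100/µl after, a fall of 1 − 100/2100 = 95 %. Innate cells are relatively spared, with no counts given.

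**Assumptions, not in the document.** CD4 T cells are 45 % of lymphocytes at both times: 0.45 × 2100 = 945/µl and 0.45 × 100 = 45/µl. After CD14/CD56 exclusion, c non-T cells/µl remain in the CD4 gate. For a later visit with partial repopulation, 300 CD4 T cells/µl is illustrative.

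**Formula.** Non-T share of the gate = c / (c + CD4 T cells).

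| Residue c (/µl) | Before: c/(c+945) | Nadir, residue unchanged: c/(c+45) | Nadir, residue halved | Later visit: c/(c+300) |
|---|---|---|---|---|
| 0 | 0 % | 0 % | 0 % | 0 % |
| 4 | 0.4 % | 8 % | 4 % | 1 % |
| 10 | 1 % | 18 % | 10 % | 3 % |
| 20 | 2 % | 31 % | 18 % | 6 % |
| 40 | 4 % | 47 % | 31 % | 12 % |
| 80 | 8 % | 64 % | 47 % | 21 % |

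If 400 CD4-bearing non-T cells/µl are assumed before any exclusion, the rows from 4 to 80 include 99 % removal (c = 4), 90 % (c = 40) and 80 % (c = 80). With no exclusion at all the shares would be 400/1345 = 30 % before and 400/445 = 90 % at the nadir, but the listed CD14 stain makes that case unlikely.

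**CD8 gate.** Assume CD8 T cells are 25 % of lymphocytes (525 and 25/µl) and 70 CD8-bearing non-T cells/µl. With 90 % removed, the share goes from 7/532 = 1 % to 7/32 = 22 %; with 99 % removed, from 0.7/525.7 = 0.1 % to 0.7/25.7 = 3 %. The main candidates here are NK cells, which CD56 addresses, so the case is weaker than for CD4.

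**From loaded to migrated cells.** These shares describe the loaded cells. Loading a fixed number of PBMC scales both cell types equally and leaves the share unchanged. Unequal losses in gradient isolation or freezing, and unequal migration, do change it. If non-T cells cross m times as readily as T cells, c becomes m × c: at half the rate, for example, the c = 40 row becomes the c = 20 row. The document gives no basis for m.

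**The case against.** Much of the opposing case stands.

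- A reader might infer that every CD4-positive or CD8-positive migrated cell is counted as a T cell. The document does not say so. Table 4 speaks only of migrated cells, and CD14, CD19 and CD56 in the same stain mark the main non-T populations.
- A reader might also infer that the assay contradicts a T-cell definition set for the whole study. It does not. The CD3 definitions sit in exclusion criteria that govern screening blood counts. Other T-cell assays name subsets without CD3, for example the regulatory T cells in Table 4 item 2f and in the Suppression Assay section.
- The description is abridged: "Transmigration assays will be performed with minor modifications as described previously [34, 35". Gating may be set out in the cited methods or the full protocol, and its absence from the article is no error.
- The size is assumption throughout. Spared does not mean unchanged: the Background says dendritic cells and monocytes carry some CD52. The nadir is also the worst case, and the later-visit column is far milder.

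What the objection does not remove is the marker list itself. It is stated, not left open; it has no CD3 and no dendritic-cell marker; and no gate can recover a marker that was not stained. Nor is the vulnerable period necessarily short: the Background says CD4 cells do not reach the lower limit of normal before 35 months, in a 36-month study.

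**Conclusion.** The point holds as a limit of the listed panel: it cannot reliably separate migrated T cells from residual CD4-bearing non-T cells, and it cannot keep CD56-positive T cells while excluding NK cells. The direction follows from the plan's own expectations, provided some residue stays in the gate: its share rises after treatment and falls again with repopulation. Under the assumed residues the nadir share in loaded CD4-gated cells runs from a few per cent to roughly half or more, and it is zero with complete exclusion. Gating, residual counts and relative migration decide where in that range the study would fall, and the document gives none of them. The stronger conclusion, that the reported change in T-cell migration will be wrong, is therefore not supported. This is a minor improvement to one readout of a secondary endpoint in an openly exploratory study. It touches neither the primary endpoints nor the sample size.

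**What to change.** Add CD3 to the migration stain, apply it to both the loaded and the migrated cells, and report CD3+CD4+ and CD3+CD8+ migrated cells. This matches how the screening counts identify these cells. Stating a CD14/CD56 gate without CD3 would help, but would leave the dendritic-cell residue and the loss of CD56-positive T cells.

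The cost is one antibody per tube, one extra fluorescence channel and one added marker in the Migration Assay section. The change has to be made before samples are stained. If some have already been run, each patient's baseline and follow-up samples should be compared only under the same panel.
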